### Primary outcome

#### PSQI-K

The Pittsburgh Sleep Quality Index (PSQI) is a subjective evaluation tool for sleep quality that includes quantity, depth, and peace of sleep. Subjective sleep quality, sleep latency, sleep duration, sleep efficiency, sleep disturbance, sleep medication use, and daytime dysfunction are evaluated. Each domain has a minimum score of 0–3 points, and the total score of the seven subdomains ranges from 0 to 21 points [31]. The higher the total score, the higher the severity of the sleep disorder; if it exceeds 5 points, it is judged as a sleep disorder. In this study, the Korean version will be used that has been independently confirmed for validity and reliability [24].

The primary outcome is the difference between the treatment and placebo groups in terms of changes in the total PSQI-K score observed before taking the investigational drug, at the end of 12 weeks of medication, and after 12 weeks of 12-week medication.

### Secondary outcomes

#### PSQI-K

Changes in the total PSQI-K score observed before taking the investigational drug, at the end of 12 weeks of medication, and after 12 weeks of the 12-week medication in each group.

#### ISI-K

The insomnia severity index developed by Bastien et al. [32] was validated using the Korean version by Cho et al. [33]. On a scale of 0 to 4, the intensity of insomnia experienced in the previous two weeks, contentment with present sleep patterns, disruption of daily activities, distress brought on by sleep issues, and impairment of quality of life are all assessed. A score of less than 15 is categorized as a risk factor for insomnia. The total score runs from 0 to 28, with 0 being the lowest and 28 being the highest. We evaluate the ISI-K score before taking the investigational drug, at the end of the 12 weeks of medication, and after 12 weeks of 12-week medication in each group.

#### SNSB-D

The Seoul Neuropsychological Screening Battery is a test developed to evaluate cognitive function, and it is a representative Korean-style clinical scale tool consisting of tests with relatively simple instructions, performance, and standardized studies so that even the elderly with a low social education period can easily access them [25]. The SNSB-D provides a Global Cognitive Function score that sums up only the test results that can be assigned to the subtests of the five cognitive domains of the SNSB. The total score is out of 300, with 17 points for attention, 27 points for language, 150 points for memory, 36 points for visuospatial function, and 70 points for frontal/executive function. This is tested before administration of the investigational drug and at the end of 12 weeks of medication.

#### SF-36

The 36-item MOS Short Form-36 is the most widely used universal health-related QoL scale, consisting of eight domains and 36 items [27]. The physical component summary includes the following: physical functioning, physical role, bodily pain, and general health. The mental component summary includes vitality, social functioning, role emotion, and mental health. This is evaluated before taking the investigational drug, at the end of 12 weeks of medication, and after 12 weeks of 12-week medication in each group.

#### S-GDS

The short-form Geriatric Depression Scale is a 30-item Geriatric Depression Scale (GDS) developed by Yesavage et al. [34] to evaluate the level of depression and anxiety and has a total of 15 questionnaire items. A score of ≥ 8 indicates a depressed state, while a higher score indicates a severely depressed state. In this study, the Korean version standardized by Bae et al. (2004) [28] will be used before taking the investigational drug and at the end of the 12 weeks of medication.

### Safety assessments and monitoring

Adverse events will be investigated during each visit. Subjects who took the investigational drug at least once are eligible for safety analysis. Any undesirable medical findings indicating symptoms not observed prior to the study are considered adverse events.

At every visit, blood pressure, pulse rate, and body temperature are investigated to determine the participants’ health status. Laboratory tests for glucose, aspartate aminotransferase (AST), alanine aminotransferase (ALT), blood urea nitrogen (BUN), creatinine, sodium, potassium, chloride, lactate dehydrogenase (LDH), creatine phosphokinase (CPK), and electrocardiography (ECG) are investigated before taking the investigational drug and after 6 and 12 weeks of medication. Participants with abnormal laboratory test results should be followed up. Additionally, total cholesterol, HDL cholesterol, LDL cholesterol, triglyceride, homocysteine, T3, free T4, and thyroid stimulating hormone (TSH) levels are investigated at baseline.

After visit 1 (baseline), the investigators monitor status of medication, adverse events, and concomitant medications via phone calls once a week until the next visit. After the end of the medication at visit 3 (12 weeks), the investigators monitor adverse events and concomitant medications via phone call every two weeks until the final visit.

### Concomitant medication

It can be allowed at the discretion of the investigators if it does not fall under the prohibited drug category among the drugs taken at least 2 weeks before participating in the study. Drugs used for the transient treatment of other diseases should be administered in consultation with the investigators. For all other drugs, information (product name, purpose of administration, duration, dosage, etc.) are recorded in a case report form.

Drugs and non-pharmacological treatments that may improve insomnia or affect cognitive function are prohibited. If the participants have taken these drugs or received treatment during the medication period, the study will be discontinued.

### Sample size

The herbal medicine, Kami Guibi-tang (KGT), used in this study is already approved for insomnia by the Korean Food and Drug Administration. This study aimed to evaluate insomnia in older adults and assess cognitive function. According to the central limit theorem, a sample consisting of > 30 individuals per group is assumed to be normally distributed; therefore, the sample size for this study was 30 individuals per group. If the normality test confirms that the distribution is normal, we will perform statistical analysis parametrically [35].

### Statistical analysis

All statistical analyses is a two-sided and the significance level is set at 5%. Statistical program SPSS (Ver 25.0 or more updated, IBM Corporation) will be used as the primary analysis tool. All participants randomized according to the intent-to-treat (ITT) analysis principle are considered as the Full Analysis Set (FAS). Participants who have completed taking investigational product for 12 weeks and completed up to the follow-up period (week 24) after 12 weeks are referred to as the protocol compliance analysis group, as per-protocol (PP).

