#### Drop-out criteria

The investigators will discontinue the administration of the investigational drug and drop the subjects according to the dropout criteria. The subjects can also voluntarily withdraw from the trial at any time. The criteria for dropout are as follows:When a serious adverse event occurs or when the participant requests discontinuation of the study due to an adverse event.When a systemic disease is found that was not detected in the examination prior to the administration of the investigational drug.In case the participant or the participant’s legal representative requests to discontinue the study.The medication compliance is < 60% at visit 2 (6 weeks after taking the investigational drug).The medication compliance is < 80% at visit 3 (12 weeks after taking the investigational drug).When the participant withdraws consent to participate in the clinical trial.In case the participant is not tracked.In the case of taking drugs that may affect the study results without the investigators’ instruction or consent during the study period.In other cases where the investigators determine that it is inappropriate to proceed with the study.

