### Intervention

KGT or placebo granules (one dose: 3.0 g) are orally administered with water 3 times a day (30 min after meals) for 12 weeks. KGT is a herbal medicine approved by the Ministry of Food and Drug Safety and is manufactured by Kyoung Bang Pharmaceutical Co., Ltd. (Incheon, Republic of Korea). It is yellow-brown granules and consists of *Astragali Radix* 1.0 g, *Ginseng Radix* 1.0 g, *Atratylodis Rhizoma* 1.0 g, *Poria* 1.0 g, *Zizyphi Fructus* 0.67 g, *Zingiberis Rhizoma* 0.33 g, *Saussureae Radix* 0.33 g, *Glycyrrhizae Radix* 0.33 g, *Zizyphi Spinosi Semen* 1.0 g, *Longan Arillus* 1.0 g, *Angelicae Radix* 0.67 g, *Polygalae Radix* 0.67 g, *Bupleuri Radix* 1.0 g, *Moutan Radicis Cortex* 0.67 g, and *Gardeniae Fructus* 0.67 g. The placebo was manufactured at the National Institute for Korean Medicine Development (NIKOM) Herbal Medicine Production Center (GMP) in Daegu, Republic of Korea, with an appearance, taste, and smell similar to KGT.

The participants will be trained to take the drug three times a day and then return the remaining medication at their next visit. Regarding compliance with the investigational drug, the remaining drug brought in by the participant at the time of the next visit is identified and recorded on a case report form. Medication compliance (%) signifies that the participant’s actual dose is divided by the number of investigational drugs taken by the date of the participant’s visit based on the date of the last visit × 100. The actual dose is the number of returned drugs on the day of the participant’s visit, subtracted from the drugs provided to the participant. When visiting 6 weeks after taking the drugs, the investigator retrieves the unused dose and reversely check the total dose. If medication compliance is less than 60% at the 6th week of taking, the subject will drop out. Even if all doses were administered over the next 6 weeks, the final medication compliance is < 80%. The final medication compliance must be 80% or higher; if medication compliance is less than 80%, the participant is excluded from the per-protocol (PP) analysis group.

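### Compliance below 80% at visit 3 drops the participant in one section but only removes them from PP in another, leaving week-24 primary data in doubt

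*Protocol article*

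**What the plan says.** Four places in the protocol article bear on this.

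- **Drop-out criteria** states the general effect: "The investigators will discontinue the administration of the investigational drug and drop the subjects according to the dropout criteria". Two of the listed criteria concern compliance: "The medication compliance is < 60% at visit 2 (6 weeks after taking the investigational drug") and "The medication compliance is < 80% at visit 3 (12 weeks after taking the investigational drug").
- **Intervention** gives the same consequence as Drop-out criteria at week 6: "If medication compliance is less than 60% at the 6th week of taking, the subject will drop out". For the final figure it names a different one: "if medication compliance is less than 80%, the participant is excluded from the per-protocol (PP) analysis group". It does not mention dropping out at that point.
- **Statistical analysis** defines the main set, "All participants randomized according to the intent-to-treat (ITT) analysis principle are considered as the Full Analysis Set (FAS"), and then PP, "Participants who have completed taking investigational product for 12 weeks and completed up to the follow-up period (week 24) after 12 weeks". The PP definition has no compliance percentage.
- **Efficacy analysis** bases efficacy on the FAS, with PP in support. It admits anyone with a baseline and at least one later PSQI-K, and analyses change at weeks 12 and 24 by repeated measures ANOVA (RM ANOVA) and a linear mixed model (LMM).

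Safety assessments and monitoring places the end of medication at visit 3 (week 12) and plans two-weekly calls about adverse events and concomitant medication from then to the final visit.

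**The concern.** At week 6 the two sections agree. At visit 3 they do not: one drops the participant and the other only changes an analysis set. Whether a week-24 score is collected from these participants therefore depends on which section the site follows.

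If Drop-out criteria is followed, missing week-24 data are created by rule, and the rule turns on adherence, which is observed after randomisation and may itself be affected by treatment. That works against the intention-to-treat principle on which the FAS is defined, and it does so at one of the two primary time points. A score that was never collected cannot be recovered by a later choice of analysis.

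**Working it through.** **1. The plan's own compliance arithmetic.** Intervention says that a participant below 60% at week 6 must finish below 80% even if every later dose is taken. Inputs: three doses a day for 12 weeks (Intervention).

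- Doses per half: 3 × 42 = 126. Total: 3 × 84 = 252.
- Best final compliance = (week-6 doses + 126) / 252.
- At exactly 60%: (75.6 + 126) / 252 = 80.0%.
- Highest whole count below 60%: 75/126, giving (75 + 126) / 252 = 201/252 = 79.8%.

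The statement reproduces. It also shows that the 80% limit is cumulative, and I read the visit-3 criterion in the same way. The visit-3 criterion therefore catches people who passed week 6 and then ended on 201 doses or fewer.

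**2. One participant under each section.** Take 190 of 252 doses (190/252 = 75.4%), at least 60% at week 6, and willing to attend week 24.

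| Section followed | Week-24 PSQI-K | In PP? |
|---|---|---|
| Drop-out criteria | Not collected (dropped at week 12) | No, week 24 not completed |
| Intervention | Can be collected | No, below 80% |
| Statistical analysis, read with Intervention | Can be collected | No |

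PP membership is the same in every row. What changes is whether week-24 data exist.

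**3. What a drop at visit 3 can do.** Medication has ended by then, so no dosing is left to stop. The drop can only end follow-up. By the schedules in Outcome measurements and in Safety assessments and monitoring, that removes the week-24 PSQI-K, ISI-K and SF-36 and the post-treatment calls. This takes dropping a subject to mean that assessments cease; the article nowhere says that they continue.

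**4. Effect on the primary analysis.**

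- *LMM:* the week-12 score is kept if it was taken at visit 3, but the week-24 comparison rests only on people at or above 80%, plus the model's missing-data assumption.
- *RM ANOVA:* in its usual form it needs every time point, so the same participant is lost at week 12 as well, although Efficacy analysis admits anyone with one later score.

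**5. Size.** The article gives no non-compliance rate. Assume 5% to 15% of 60, spread evenly over two arms of 30, with no other loss and an unchanged standard deviation.

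- Participants affected: 0.05 × 60 = 3; 0.15 × 60 = 9.
- Left per arm at week 24: 30 × 0.95 = 28.5; 30 × 0.85 = 25.5.
- Standard error relative to 30 per arm: √(30/28.5) = 1.026; √(30/25.5) = 1.085.

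The loss of precision is about 3% to 8%. The selection by adherence is the more serious effect, and the article gives no data from which to size it.

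**The case against.** The strongest reply is that this is a condensed article whose sections can be read together. Intervention does not say that a participant below 80% stays in follow-up; that is implied by the contrast with the week-6 rule. PP is supportive only, and a participant dropped at visit 3 can still enter the FAS through the week-12 score. The full protocol may say what happens to data after a drop.

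Much of this stands, and it rules out several stronger readings that a reader might infer.

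- *That the plan treats these participants in three different ways, one of them inside PP.* Statistical analysis does not address a participant below 80%. Placing them inside PP is an inference from its silence, and Intervention can be read as an added condition.
- *That the make-up of PP is in dispute.* Read together, all the sections put the participant outside PP.
- *That comparing FAS with PP would show nothing.* At week 12 under the LMM the two sets still differ.
- *That requiring week 24 for PP at week 12 is an error.* A PP set of people who completed the whole period is conventional; applying PP visit by visit is a preference.

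The reply does not remove the direct conflict. The drop at visit 3 is stated in print ("The medication compliance is < 80% at visit 3"), and it differs from the consequence stated in Intervention. This is a stated rule rather than omitted detail.

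**Conclusion.** The point holds as a conflict between Drop-out criteria and Intervention over a participant below 80% at visit 3. Followed as written, Drop-out criteria leaves the all-randomised FAS with no week-24 data from such participants, and RM ANOVA on complete cases would lose their week-12 score too. The missing 80% condition in the PP definition is a secondary misalignment.

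On the assumed 5% to 15%, this concerns 3 to 9 of 60 participants. The conclusion rests on two readings: that visit-3 compliance is the cumulative figure, and that a dropped subject has no further assessments. It is worth correcting because it touches a primary time point in the main analysis set. It does not show that the PP results or the week-12 LMM comparison are unsound.

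**What to change.** Reconcile Drop-out criteria with Intervention so that compliance below 80% at visit 3 affects PP membership only and does not end outcome collection. Continue the planned week-24 assessments and the post-treatment calls for these participants, unless consent is withdrawn or they cannot be traced, and analyse them in the FAS. Add the 80% condition from Intervention to the PP definition in Statistical analysis, so that PP is defined once.

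No change to dosing or to any treatment-stopping rule is proposed.

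The cost is an amendment through the ethics approval route that the Discussion already describes for changes, and a few more follow-up visits in non-compliers. Trial status reports eight participants enrolled at 25 August 2023, with recruitment planned to October 2024, so at that date the change could still have covered most of the trial.

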#### Efficacy analysis

Efficacy evaluation is based on the FAS analysis group, and efficacy is analyzed and presented with reference to the PP analysis group. For safety evaluation, the ITT analysis group is the main assay.

Analysis of primary efficacy endpoints.

Participants with PSQI-K scores before the study and at least once after consuming the investigational product are analyzed. Based on the baseline, the difference between the two groups in the total PSQI-K score change at weeks 12 and 24 is analyzed using repeated measures analysis of variance (RM ANOVA) and linear mixed model (LMM) methods.

2)Analysis of secondary endpoints.

The PSQI-K score change will be analyzed by a paired t-test within each group for changes at 12 and 24 weeks based on the baseline. The ISI-K score change will be analyzed using the paired t-test within each group and the independent t-test between the two groups at the 12-week dosing period and at 24 weeks based on the baseline. The SNSB-D and S-GDS score changes will be analyzed using the paired t-test within each group and the independent t-test between the two groups with respect to the score change at week 12, based on the baseline. The SF-36 score change will be analyzed using a paired t-test within each group and an independent t-test between the two groups at 12 and 24 weeks based on the baseline. Changes over time will be analyzed using the RM ANOVA and LMM methods. The estimated values of the mean difference between the groups, 95% confidence intervals, and p-values will be presented.

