### Outcome measurements

The PSQI-K and ISI-K are evaluated to confirm the effect of KGT granules on insomnia in the elderly. This will be measured three times: before taking the investigational drug, at the end of 12 weeks of medication, and after 12 weeks of 12-week medication.

To evaluate cognitive function, the SNSB-D is measured twice: at screening and at the end of 12 weeks of medication. In addition, to evaluate quality of life, SF-36 is measured three times: before taking the investigational drug, at the end of 12 weeks of medication, and after 12 weeks of the 12-week medication. The S-GDS, which evaluates depression, is measured twice in total: before taking the investigational drug and at the end of 12 weeks of medication.

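### The full analysis set is declared as all randomised participants, but the drop-out rules and the post-dose PSQI-K requirement take anyone dropped before week 12 out of the primary analysis

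*Protocol article*

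**What the plan says.** **Analysis set.** Statistical analysis section: "All participants randomized according to the intent-to-treat (ITT) analysis principle are considered as the Full Analysis Set (FAS". Efficacy analysis section: "Efficacy evaluation is based on the FAS analysis group", with the per-protocol (PP) set for reference. The paragraph on the primary endpoint then narrows this: "Participants with PSQI-K scores before the study and at least once after consuming the investigational product are analyzed". Two methods are named for that endpoint, RM ANOVA and a linear mixed model (LMM), and neither is ranked first.

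**Timing of the outcome.** Outcome measurements section: PSQI-K is recorded "before taking the investigational drug, at the end of 12 weeks of medication, and after 12 weeks of 12-week medication". There is no week-6 value.

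**Drop-out.** Drop-out criteria section: "The investigators will discontinue the administration of the investigational drug and drop the subjects according to the dropout criteria". One trigger reads "The medication compliance is < 60% at visit 2 (6 weeks after taking the investigational drug". Others are a serious adverse event, compliance below 80% at visit 3 (week 12), and unapproved use during the study period of drugs that could affect the results. The Concomitant medication section adds, for prohibited treatments: "If the participants have taken these drugs or received treatment during the medication period, the study will be discontinued".

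**Compliance below 80%.** The Intervention section gives a different consequence from the Drop-out criteria section: "if medication compliance is less than 80%, the participant is excluded from the per-protocol (PP) analysis group".

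**The concern.** A participant who meets a drop-out criterion before week 12 is dropped as well as taken off product, and the article describes no assessment afterwards. That person has a baseline PSQI-K and nothing else, fails the post-dose requirement, and is absent from an analysis described as intention-to-treat.

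These removals happen after randomisation and may be linked to outcome. People who tolerate the granules badly may skip doses. People who sleep badly may start a sleep aid, and sleep medication use is one of the seven PSQI domains, so the rule can remove a participant for something the primary endpoint itself scores. The weekly phone calls up to week 12 ask about concomitant medication, so such use is likely to be found. If the arms lose different numbers or different kinds of participants, the primary comparison is no longer between the groups as randomised.

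**Working it through.** **1. The plan's own arithmetic.** The Intervention section says that a participant below 60% at week 6 cannot reach 80% overall. With equal six-week halves, final compliance = (first half + second half) / 2.
- 60% then 100%: (60 + 100) / 2 = 80.0%
- 59% then 100%: (59 + 100) / 2 = 79.5%
- 70% then 70%: (70 + 70) / 2 = 70%

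The statement is correct. The last case passes the week-6 check and is caught only at visit 3, the visit at which the week-12 PSQI-K is due.

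**2. Who leaves which analysis.** This applies the drop-out rules to the PSQI-K schedule, taking the article's silence on later assessments at face value.

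| Reason | Week-12 score | Week-24 score | LMM | Listwise RM ANOVA |
|---|---|---|---|---|
| Compliance below 60% at week 6 | no | no | out | out |
| Prohibited treatment or serious adverse event before week 12 | no | no | out | out |
| Compliance below 80% at visit 3, Drop-out criteria section applied | possible | no | in, if scored at week 12 | out |
| Compliance below 80% at visit 3, only the PP exclusion applied | yes | yes | in | in |
| Unapproved drug use in weeks 12 to 24 | yes | no | in | out |

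The first two rows are lost under either method. The third and fifth depend on the method, and the third and fourth differ only by which section is followed.

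**3. Possible bias, in SD units.** The article gives no drop-out rates, so these are assumptions. Suppose there is no true effect and, in each arm, the fraction p with the highest drop-out propensity is removed. Let that propensity be standard normal with correlation r to the outcome. The mean of those retained shifts by r × φ(z) / (1 − p), where z is the normal quantile that cuts off the top p.
- p = 5%: 0.103 / 0.95 = 0.109
- p = 20%: 0.280 / 0.80 = 0.350
- p = 10%: 0.175 / 0.90 = 0.195
- p = 30%: 0.348 / 0.70 = 0.497

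Bias is r times the difference between arms.
- 20% versus 5%: 0.350 − 0.109 = 0.241, giving 0.07, 0.12 and 0.19 SD at r = 0.3, 0.5 and 0.8
- 30% versus 10%: 0.497 − 0.195 = 0.302, giving 0.09, 0.15 and 0.24 SD
- equal removal at the same r: 0

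The arm that loses more participants looks better.

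**4. The same in PSQI-K points.** If removed participants do g points worse than retained ones, an arm's mean improves by p × g on removal.
- 20% versus 10%, g = 2 to 4: (0.20 − 0.10) × g = 0.2 to 0.4 points
- 30% versus 10%, g = 2 to 4: (0.30 − 0.10) × g = 0.4 to 0.8 points
- equal removal and equal g: 0

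Equal removal alone is not enough. With 20% removed in each arm but g = 4 in one and 2 in the other, the shift is 0.20 × 4 − 0.20 × 2 = 0.4 points.

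**The case against.** **Compliant completers.** A reader might infer that the primary analysis amounts to compliant completers only, that the FAS and PP sets nearly coincide, and that week 24 describes compliers alone. The article does not support this. The primary analysis asks for one post-dose score, not for completion or compliance. The LMM can keep participants with 60% to 79% compliance or without week 24, whereas PP needs 12 weeks of product, follow-up to week 24 and at least 80% compliance. The completer label fits only listwise RM ANOVA. The week-24 claim also assumes that the drop-out rule for compliance below 80% prevails over the Intervention section, which is unsettled.

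**Timing and scope of the rules.** Not every rule acts before the first post-baseline score: the 80% rule acts at the week-12 visit, and the drug rule runs on to week 24. That rule covers use without the investigators' agreement, and the Discussion allows enrolment on unchanged sleeping pills, so the mechanism concerns new or changed use. Both limits stand.

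**Size.** One could set 0.24 SD against the effect detectable with 80% power at 30 per arm, (1.960 + 0.842) × √(2/30) = 0.72 SD, and call the bias a third of it. That takes the most extreme assumed case. The trial is double-blind with a matched placebo, and loss may be balanced.

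**A condensed article.** The full protocol may provide for assessments after discontinuation. If so, the loss before week 12 shrinks, but the conflicting statements on the analysis set and on the 80% rule remain.

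**The remedy.** A participant with only a baseline adds almost nothing to a week-12 or week-24 contrast in any mixed model. Deleting the post-dose requirement without collecting more data would be close to cosmetic. This also stands and shapes the fix.

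**Conclusion.** The concern holds in a limited form. The declared all-randomised FAS and the population analysed for the primary endpoint differ. On the article's text, participants dropped before week 12 are lost from both RM ANOVA and the LMM, for post-randomisation reasons that may relate to response or tolerability. Those dropped at or after week 12 can remain in the LMM through a week-12 score but lose week 24, which is part of the primary outcome, and fall out of listwise RM ANOVA. Separately, two sections attach different consequences to compliance below 80%.

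Neither the size nor the direction of bias follows from the document. The range of 0.07 to 0.24 SD rests on assumed unequal removal and assumed correlations of 0.3 to 0.8, and bias is zero with equal removal and equal gaps. The conclusion on who is lost assumes that dropped participants are not assessed later. It matters now because outcomes never measured cannot be recovered, and the article reports eight participants enrolled of a planned 60.

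**What to change.** 1. Leave the rules for stopping the investigational product as they are, but state that stopping product is not leaving the study. Ask every randomised participant who has not withdrawn consent for PSQI-K, ISI-K and SF-36 at the existing week-12 and week-24 visits, whatever their compliance or concomitant drug use. This is the part that reduces bias.
2. Make the primary analysis a likelihood-based mixed model on all randomised participants with their available data, in place of listwise RM ANOVA, and say how scores recorded after prohibited drug use are handled.
3. Reconcile the FAS definition in the Statistical analysis section with the primary-endpoint paragraph under Efficacy analysis, so that one population is stated.
4. Reconcile the Drop-out criteria and Intervention sections on what follows from compliance below 80%. The documents do not settle which applies, and that is for the sponsor to decide.

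The cost is a small amendment, a few extra attendances at visits already scheduled, and possibly a slightly smaller estimated effect because non-compliers are included.
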